## Abstract

**Background:**

Early marriage and early childbearing are highly prevalent in Niger with 75% of girls married before age 18 years and 42% of girls giving birth between ages 15 and 18 years. In 2012, only 7% of all 15–19-year-old married adolescents (male and female) reported use of a modern contraceptive method with barriers including misinformation, and social norms unsupportive of contraception. To meet the needs of married adolescents and their husbands in Niger, the Reaching Married Adolescents (RMA) program was developed with the goal of improving modern contraceptive method uptake in the Dosso region of Niger.

**Methods:**

Using a four-arm cluster randomized control design, the RMA study seeks to assess whether household visits only (Arm 1), small group discussions only (Arm 2), or a combination of both (Arm 3), as compared to controls (no intervention – Arm 4), improve modern contraceptive method use among married adolescent girls and young women (AGYW), age 13–19 years-old, in three districts of the Dosso region. Intervention conditions were randomly assigned across the three districts, Dosso, Doutchi, and Loga. Within each district, eligible villages were assigned to either that intervention condition or to the control condition (12 intervention and 4 control per district). Across the three intervention conditions, community dialogues regarding modern contraceptive use were also implemented. Data for the study was collected at baseline (April – June 2016), at 24 months post-intervention (April – June 2018), and a final round of data collection will occur at 40 months post-intervention (October – December 2019).

**Discussion:**

The RMA intervention is a gender-synchronized and community-based program implemented among married adolescent girls and their husbands in the context of rural Niger. The intervention is designed to provide education about modern contraception and to promote gender equity in order to increase uptake of modern contraceptive methods. Results from this cluster randomized control study will contribute to the knowledge base regarding the utility of male engagement as a strategy within community-level approaches to promote modern contraceptive method use in the high need context of West Africa.

**Trial registration:**

Registered October 2017 - ClinicalTrials.gov NCT03226730.

## Plain English summary

In Niger, early marriage is common, but family planning is not generally practiced leading to significant early childbearing and increasing the health risks for young married girls. To meet the needs of these young married girls, the Reaching Married Adolescents (RMA) program was designed with the goal of improving use of modern contraceptive methods. Three districts of the Dosso region of Niger were randomly assigned to receive one of three intervention approaches: 1) small group discussions, to strengthen social bonds, 2) household visits, to provide knowledge about reproductive health and family planning, or 3) a combination of small group discussions and household visits. From these three districts, 48 villages were randomly selected (12 participating in the intervention approach assigned to the respective district and 4 to serve as a control). Villages that were selected to participate in the intervention also participated in community dialogue sessions to create an environment supportive of family planning and healthy timing and spacing of pregnancy. From each village, 25 married adolescent girls (ages 13–19) and their husbands were randomly selected to participate. Data for the study was collected at pre-intervention implementation (April – June 2016), at 24 months post-intervention implementation (April – June 2018), and a final round of data collection will occur at 40 months post-intervention implementation (October – December 2019). Results from this study will contribute to the knowledge base regarding the utility of involving men as a strategy within community-based programs to promote modern contraceptive method use in the high need context of West Africa.

## Background

Recent Demographic and Health Survey (DHS) data from Niger show that 76% of girls marry before the age of 18 and 28% before the age of 15 [1]. Though marrying under age 18 years is permitted by law (legal age of marriage is 15 years for girls) [2], child marriage is associated with poor adolescent health and development, including neonatal and maternal mortality, lack of formal education, and intimate partner violence (IPV). Child marriage is also associated with early childbearing and high adolescent fertility in Niger and multiple other contexts [3–5]. Approximately 9% of girls give birth to a child before age 15 years and 42% give birth between ages 15 and 18 years in this West African nation, [6] with adolescent and total fertility in Niger higher than any country globally [7].

Girls who marry at younger ages in Niger are less likely than those marrying at older ages to utilize maternal health care services (e.g., antenatal visits and institutional delivery), contributing to poor health outcomes [8]. In 2012 in Niger, only 7% of all 15–19 year-old married adolescents (male and female) reported use of a modern contraceptive method [9]. Barriers to modern contraceptive use include lack of access, lack of awareness, misinformation and lack of knowledge, and opposition to use by partners and family [9]. Multiple social norms (i.e., shared social expectations) have been documented in this and other sub-Saharan cultural contexts that additionally impede modern contraceptive uptake [10]. Programs designed to combat early and frequent childbearing in these regions by promoting modern contraceptive use face the challenge of addressing these many barriers.

To meet the needs of married adolescents and their husbands in Niger, Pathfinder International (Pathfinder) developed an intervention aimed at improving modern contraceptive method uptake in the Dosso region of Niger. The Reaching Married Adolescents (RMA) program focuses on increasing knowledge of modern contraceptive methods and changing relevant attitudes and norms that may impede use via household visits and small group discussions with married adolescent girls and young women (AGYW) and their husbands. Complementing the focus on contraceptive use, this gender-synchronized approach also engages men and women to challenge gender norms and adopt attitudes supportive of gender equity, particularly with respect to female autonomy and decision-making regarding sexual and reproductive health (SRH). Researchers from the Center on Gender Equity and Health at the University of California, San Diego (UCSD) [11] are carrying out a cluster randomized control trial of this intervention to assess its impact on both modern contraceptive use and relevant gender equity outcomes.

### Study overview and design

The purpose of the RMA evaluation study is to assess the efficacy of the RMA intervention using a four-arm cluster randomized control design (October 7, 2017, retrospectively registered, https://clinicaltrials.gov/ct2/show/NCT03226730, Clinical Trials ID: NCT03226730). Specifically, this study seeks to assess whether household visits only (Arm 1), small group discussions only (Arm 2), or a combination of both (Arm 3), as compared to controls (no intervention – Arm 4), improve modern contraceptive method use among married AGYW, age 13–19 years-old, in three districts of the Dosso region of Niger. Based on our conceptual model, we hypothesize that married AGYW that participate in any of the three intervention arms will report: 1) improvement in knowledge of modern contraceptive methods, 2) attitudes more supportive of contraceptive use and gender equity, 3) perceived norms within their communities as more supportive of contraceptive use and gender equity, 4) increased self-efficacy to use a contraceptive method, 5) intention to use a modern contraceptive method, 6) reduction in IPV, and 7) increased use of modern contraceptive methods. Secondarily, reflective of the male engagement elements of RMA, we hypothesize that higher levels of participation of husbands of married AGYW will be associated with greater increases in modern contraceptive use and greater reductions in intimate partner violence, relative to lower levels of husband participation or no participation at all.

Quantitative baseline data (pre-intervention) were collected from April–June 2016 using structured surveys. These same data are collected at 24 months post-baseline (Time 2) from April – June 2018, and 40 months post-baseline (Time 3) from October – December 2019 (see Fig. 1).

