#### District randomization, village selection, and randomization

The Ministry of Health chose the Dosso region of Niger for the RMA intervention. This region has five districts from which three districts, Dosso, Doutchi, and Loga, were selected for participation. Based on the logistical challenges of providing all RMA intervention approaches in each district, each district was randomly assigned to one of the three intervention approaches (home visits alone, small groups alone, or a combination), with controls selected across all three districts. Based on power analyses (described below), the minimum number of clusters in each of the four arms was 12, requiring inclusion of 16 villages across each of the three districts (12 intervention and 4 control). Village selection and randomization followed a multi-stage process whereby eligible villages in the three districts were first identified based on the following criteria: 1) rural (i.e., not designated as a market town or city), 2) Hausa- or Zarma-speaking, 3) a minimum of 1000 inhabitants, and 4) located within 5 km of a *centre de santé intégré* (CSI) or *case de santé* (CS) health facility. There were 101 villages in Dosso, 110 in Doutchi, and 36 in Loga that met these criteria. From the eligible villages, we then stratified villages based on three level of health service provision: 1) villages with CSIs, larger health facilities serving multiple villages where doctors, nurses, and midwives provide the full contraceptive method mix and related counseling; 2) villages with CSs, village-level facilities where community health agents provide a subset of contraceptive methods; and 3) villages with neither CSI nor CS. Among the 247 total eligible villages across the three districts, 21% had a CSI, 56% had a CS, and 23% had neither. In order to select a sample of villages within each district that was representative of the distribution of health facilities across the region, we randomly selected nine villages with a CS, three with a CSI, and four with neither in each of the three districts. To create a control arm representative of villages in each district, and that included representation of all levels of health facility, we randomly assigned four of the total 16 villages per district to the control condition, consisting of two villages with a CS, 1 with a CSI, and 1 with neither. The remaining 12 villages were assigned to the intervention condition assigned to that district (see Fig. 3).

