#### Power

Power calculations for our study were conducted a priori based on our primary outcome of interest, modern contraceptive method use (reported by the adolescent wives in our sample). We used pairwise tests for time by treatment effects comparing each intervention group individually to the control group. We chose to account for a moderate intra-cluster correlation coefficient – kappa = 0.05 and an attrition rate of 10%. We also chose to account for the ability to detect an effect size of 2.0 greater odds of contraceptive method use, based on literature reviews of evaluations of interventions seeking to improve contraceptive use, as well as our own experience conducting such trials in other regions. Four arms with 12 clusters nested within each arm, and a sample size of 240 couples per arm (300 couples at baseline with 20% expected attrition; 1200 total baseline participating couples) was calculated to provide 80% power to detect associations of this magnitude.

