Supplementary Intervention Component	Community Dialogues	Community gatekeepers including traditional and community leaders, parents and in-laws participate in community dialogue and reflection sessions to create an environment supportive of HTSP and contraception use.	Four community facilitators (FACOMs) in each district, 1x/month	Loga, Dosso, Doutchi

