##### Supplementary intervention component: community dialogues

Community dialogues supplement the two main intervention approaches, household visits and small group discussions, and are a constant in all three intervention arms. Once each month in every intervention village, all adolescent and adult members of the community gather to participate in community dialogue and reflection sessions. This activity is meant to create an environment supportive of modern contraceptive method use and HTSP. Town criers alert community members to these gatherings and village chiefs and religious leaders encourage participation. Sessions are held in the village mosque or center of the village.

Community dialogue facilitators (FACOMs) who lead these sessions - four FACOMs per district (12 in total) - are a mix of men and women selected at the district level by district-level health staff and project staff. Selection of FACOMs also includes input from village leaders. Criteria for selection were the same as for *relais* and mentors. FACOMs receive a seven-day training that, similar to the training of mentors, includes modules on leading and facilitating group discussions related to gender equity, the reproductive system, modern contraceptive methods, and HTSP.

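### Arms 1 and 2 are described as single-component arms, but both also receive monthly community dialogues that controls do not, so no planned randomised contrast isolates household visits or small groups

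*Protocol article*

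**What the plan says.** Three places in the protocol article describe Arms 1 and 2 as single-component arms. Study overview and design says that "this study seeks to assess whether household visits only (Arm 1), small group discussions only (Arm 2), or a combination of both (Arm 3), as" against controls receiving no intervention, raise modern contraceptive use, and the Abstract (Methods) words the aim in the same way. The section on district randomization and village selection describes the approaches as "home visits alone, small groups alone, or a combination".

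Other places describe an additional element. The Abstract adds: "Across the three intervention conditions, community dialogues regarding modern contraceptive use were also implemented". The section on community dialogues calls them constant over the three intervention arms and says: "Once each month in every intervention village, all adolescent and adult members of the community gather to participate in community dialogue and reflection sessions". Their stated aim is to make the village setting favourable to modern contraception and to spacing of births. Table 1 lists them as a supplementary component in all three districts but gives a different audience: "Community gatekeepers including traditional and community leaders, parents and in-laws participate in community dialogue and reflection sessions".

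The Power section says that the tests are pairwise time-by-treatment effects, "comparing each intervention group individually to the control group". Planned analytic approach specifies a model with time, arm, district, selected covariates and a time-by-treatment interaction.

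**The concern.** The question as worded is whether visits by themselves, or groups by themselves, raise contraceptive use. No village receives either by itself. The dialogues are aimed at the primary outcome. Their facilitators have seven days of training on group discussion of gender equity, the reproductive system, modern methods and birth spacing, which the article likens to the five-day training of small-group mentors. They cannot be assumed to have no effect.

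An element shared by all intervention arms cancels when those arms are compared with each other. It does not cancel against a control arm that lacks it, and that is the comparison planned. A positive Arm 1 result, read under its present label, would be taken as evidence for visits alone, which were not tested. The Discussion says results will go to the Ministry of Health to inform a scale-up decision, so what an arm's effect is credited to has practical weight.

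**Working it through.** The plan gives no figure to reproduce. The check sets arm content against the planned contrasts.

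**Content of each arm** (Study overview and design; Table 1; section on community dialogues)

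| Arm | District | Visits | Groups | Dialogues |
|---|---|---|---|---|
| 1 | Loga | yes | no | yes |
| 2 | Doutchi | no | yes | yes |
| 3 | Dosso | yes | yes | yes |
| 4 (control) | 4 villages in each district | no | no | no |

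The control row follows from the no-intervention label together with the statement that dialogues take place in intervention villages. Table 1 lists dialogues by district, and control villages lie in the same districts, so spillover is possible, but it is not planned.

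**What each planned contrast estimates.** Let v, g and d be the effects of visits, groups and dialogues on the log-odds scale, taken as additive for simplicity.

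- Arm 1 − control = v + d
- Arm 2 − control = g + d
- Arm 3 − control = v + g + d

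These are three equations in three unknowns. If additivity held exactly, d could be solved as (Arm 1) + (Arm 2) − (Arm 3). That needs no interaction between components and no difference in effect between districts; the article states neither and plans no such calculation. Without additivity, Arm 1 − control is still the effect of visits given alongside dialogues plus the effect of dialogues.

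**Contrasts between intervention arms.** Arm 3 − Arm 1 would give g, and Arm 3 − Arm 2 would give v, with d cancelling. The article specifies neither. Each approach occupies one district, so such a difference also compares districts.

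**Illustration of size (the dialogue effect is assumed).** If the arm-versus-control odds ratio equals the design value of 2.0 (Power section), the component's own odds ratio is 2.0 divided by the dialogue odds ratio:

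- dialogue 1.25: 2.0 / 1.25 = 1.60
- dialogue 1.5: 2.0 / 1.5 = 1.33
- dialogue 2.0: 2.0 / 2.0 = 1.00

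**Chance of a significant arm result when the named component does nothing.** Inputs from the Power section are 240 couples in 12 villages per arm (20 per village) and an intra-cluster correlation of 0.05. The design effect is 1 + 19 × 0.05 = 1.95, so the effective number per arm is 240 / 1.95 ≈ 123. Assumed inputs are a two-sided alpha of 0.05, a control proportion of 7% or 30% (the Power section gives none), and a simple comparison of two proportions at follow-up in place of the planned mixed model.

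| Assumed dialogue odds ratio | Control 7% | Control 30% |
|---|---|---|
| 1.5 | 14% | 32% |
| 2.0 | 35% | 75% |

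These are probabilities of correctly detecting a package effect. The error would lie only in crediting that effect to the named component. The labelling point does not depend on these figures.

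**The case against.** The strongest defence is disclosure. The dialogues appear in the Abstract directly after the design description, and again in the Plain English summary, the intervention description, Table 1 and a section of their own. The article defines two primary components and calls the dialogues a supplement, so the arm labels can be read as saying which primary component an arm receives. The purpose is also stated more broadly as the efficacy of the RMA intervention, with hypotheses for any of the three arms, and package-versus-nothing contrasts answer that. All of this stands, and it shows that nothing is hidden. It does not make the words *only* and *alone* correct in the sentence that states the specific aim.

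A reader might infer more than the document supports:

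- *That no planned analysis bears on the components.* The male-engagement models compare levels of husband participation within arms that received the activity, so dialogue provision is constant there. They are observational, because participation is self-selected, but they are planned.
- *That intervention arms can never be compared.* Each district has four randomised control villages. Contrasting each arm with its own district's controls, then differencing across districts, would be possible. It would be imprecise, would assume similar effects across districts, and is not the stated model.
- *That the dialogues carry the effect.* Nothing in the article indicates this; the dialogue odds ratios above are hypothetical.
- *That Arm 1 is blurred into Arm 2.* Small groups have 10 to 13 people, are separated by sex and meet at a health center. Dialogues are village-wide gatherings. The article gives no attendance by study couples.
- *That the trial is meant to choose between approaches for scale-up.* The Discussion speaks of whether the approach is suitable for scaling, not of which one.

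**Conclusion.** The point holds for the randomised contrasts. All three planned arm-versus-control tests estimate packages that include community dialogues, and none isolates household visits or small groups. The specific aim, as worded for Arms 1 and 2, is therefore not the question that the design answers. The tests remain valid for the packages, and no sample size, model or dataset is put in doubt.

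The conclusion rests on two readings of the article: that dialogues are delivered in every intervention village, and that control villages receive none by design. It needs no assumption about how large the dialogue effect is. The two accounts of the dialogue audience, gatekeepers and family elders in Table 1 against the whole adolescent and adult community in the dedicated section, are a separate, smaller inconsistency. It matters here because it leaves open whether the study couples themselves are meant to attend.

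**What to change.** In the Abstract (Methods), Study overview and design, and the section on district randomization and village selection, restate the arms and the aim as household visits plus community dialogues, small groups plus community dialogues, and both plus community dialogues, each against no programme. Drop *only* and *alone*. The Plain English summary uses neither word for an arm and already mentions the dialogues, so it can stay as it is.

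Add one sentence saying that effects will be attributed to the packages and not to visits or groups by themselves, and that differences between intervention arms also involve different districts.

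Reconcile the dialogue audience between Table 1 and the section on community dialogues.

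The change is one of wording and needs no new data or analysis. Its cost is a narrower claim: the trial would report package effects, not effects of single components.

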**Fig. 1 Fig1:**
[figure not shown]
Study Design

#### Conceptual model

Adapted from Fishbein and Yzer’s modified Theory of Reasoned Action, [12] Fig. 2 depicts the conceptual model of the RMA intervention and the hypothesized pathways through which the intervention promotes change. The primary goal of the RMA intervention is to increase use of modern contraceptive methods among married adolescents age 13–19 years-old and their husbands in Niger. The RMA intervention provides education and counseling on use of modern contraceptive methods and the importance of delaying and spacing pregnancies, particularly for adolescents, alongside promotion of gender equitable attitudes towards, and norms regarding joint decision-making and use of modern contraception. Education on modern contraceptive methods, inclusive of reproductive anatomy and dispelling common misconceptions regarding contraceptives and fertility, is hypothesized to improve knowledge of, attitudes towards, and norms regarding contraceptive use. In parallel, promotion of gender equitable attitudes and norms is hypothesized to reduce perpetration of IPV. Research has demonstrated that IPV is associated with self-efficacy around SRH [13] thus, together, these elements are hypothesized to increase self-efficacy to use modern contraceptive methods. This in turn, will increase intention to use a modern contraceptive method finally resulting in actual modern contraceptive method use. Modern contraceptive methods promoted include intrauterine devices (IUD), injectable contraceptives, contraceptive implants, oral contraceptive pills, male condoms, female condoms, emergency contraception, and lactational amenorrhea (LAM).

